## Abstract

**Background:**

Parental cancer can have a significant impact on a family's psychosocial functioning and quality of life, whereby the children’s situation is strongly related to parental coping and capacity. Such parents ask for more help in order to increase their care capacity, while the network is often insecure about how to help and thereby withdraw. They ask for guidance and training to be able to support cancer families. Based on this, the Cancer- Psycho-Educational Program for the SOcial NEtwork (PEPSONE) study was developed.

**Objective:**

To optimize social network support through a psycho-educational program for families living with parental cancer and their network members in order to increase parental capacity and thereby secure the children’s safety and quality of life.

**Methods:**

A randomized controlled trial (RCT) in which families (N=60) living with parental cancer will be randomized to either an intervention group or a control group. The intervention will last for 3 hours and includes (1) introduction, (2) psycho-education (living with cancer in the family and the importance of social network support), and (3) discussion (this family’s need for social support). Primary outcomes are social support, mental health, and quality of life, and secondary outcomes are resilience and parental capacity. Data will be collected by a set of questionnaires distributed to healthy parents (N=60) living with a partner with cancer, one child in the family between 8-18 years of age (N=60), and network members (N=210) of the intervention families at inclusion, and after 3 and 6 months. Comparing differences between the intervention group (n=30) and the control group (n=30), the power analysis shows that *P*<.05 and a statistical power = .80 would detect effect sizes of clinical interest.

**Results:**

This paper presents the Cancer-PEPSON study’s protocol to provide a broader understanding of the background and content of the program. The study is ongoing until August 2016 and the first results are anticipated to be finished by November 2015.

**Conclusions:**

To our knowledge, this will be the first RCT study to optimize social network support through a psycho-educational program for families living with parental cancer and their network members, as well as provide an evidence basis for social network support. The results may provide important knowledge that is useful for clinical practice and further research. The trial is reported according to the CONSORT checklist.

**ClinicalTrial:**

International Standard Randomized Controlled Trial Number (ISRCTN): 15982171; http://www.controlled-trials.com/ISRCTN15982171/15982171 (Archived by WebCite at http://www.webcitation.org/6cg9zunS0)

## Introduction

Annually, approximately 30,000 Norwegians are diagnosed with cancer. Even if the majority of these are older individuals, more than 3500 children under <18 years of age experience a parent getting cancer. Thus, about 18,000 Norwegian families live with parental cancer [1,2]. Internationally, roughly 14-18% of cancer patients have dependent children, indicating a large population of families for whom cancer poses special challenges [3-5].

Social support is important for human health and quality of life, including emotional, practical and economic help, and information provided to the individual by significant others, such as distant family members, friends, and co-workers, etc [6]. Even if social support represents an essential resource for families living with parental cancer, these parents report a need for more social support and help in order to uphold their parental capacity and to continue a “normal” everyday life [7-9]. Social network members want to support and help, but request support assistance from professionals to provide them with knowledge and various strategies to facilitate better and more prolonged support [7,10]. Based on this, we developed the Cancer- Psycho-Educational Program for the SOcial NEtwork (PEPSONE) study. Cancer-PEPSONE is a randomized controlled trial (RCT) study aimed at optimizing social network support through a psycho-educational program for families and their network members, in order to uphold parental capacity and children’s quality of life. This paper presents the study’s protocol to provide a broader understanding of the background and content of the study.

### Previous Research

In a demanding balance between caring for children, work, and domestic tasks, cancer illness and cancer treatment represent a significant burden and long-lasting strain for the entire family [4,11,12]. These consequences are, however, different for individual family members.

A cancer diagnosis and treatment usually results in multiple consequences for the sick parent, including physical and psychosocial side effects, such as nausea, pain, and fatigue as well as anxiety, depression, and traumatic stress reactions [13,14]. Sick parents are, therefore, frequently challenged in fulfilling their roles in everyday life in relation to work, practical tasks at home, and caring for their children and social life [7,15]. Partners of cancer patients also experience stress reactions, anxiety, depression, and impaired quality of life [16-18]. They frequently report a considerable increase in the strain related to child care, in performing domestic tasks, and in supporting their sick partner as well as being the family’s breadwinner. Healthy partners often fulfill double roles and feel distressed, insecure, and lonely [7,11,19]. Together, these challenging strains on both parents may negatively influence their parental capacity and quality of life [12,20,21].

How children are affected by parental cancer depend on the child’s age, experiences and maturity, and the cancer severity, but are especially related to parental coping and the family’s function in everyday life [4,11,22]. Reduced parental coping negatively affects the children’s behavior and their emotional, physical, and school life [23,24]. Young children are mostly affected by concrete changes in daily routines such as frequent hospitalizations and changes in parental behaviors (eg, sadness, fatigue, and impatience) [25]. Older children and adolescents also feel empathy, and they are worried about losing their parent and think about how the cancer will influence their own futures [23,26]. These children are at risk of several physical and psychosocial symptoms such as decreased energy levels, headaches, stomach pain, sleep deprivation, concentration problems, depression, anticipatory grief reactions, and reduced quality of life [19,24]. Additionally, these children report impairments in the family’s social life and increased involvement in domestic tasks such as looking after minor siblings [23]. Research indicates that they try to reduce the strain on parents by asking for less help or not bringing friends home, as well as internalizing their own problems and concerns [23,24]. Thus, children living with parental cancer ask for predictability and stability in everyday life, and call for a balance between talking about their current situation and a “space” in which they can talk about things other than cancer, hang out with friends, and participate in leisure activities [7,27].

Several studies have emphasized the importance of social support for physical and mental health, for quality of life, as well as for coping with and recovering from cancer [28-31]. Nonetheless, cancer patients still experience disruptions in their social lives as well as unhelpful help or a lack of social support, especially over time [8,32]. Cancer patients’ main concern regards caring for their children, and in particular they want to protect their children and maintain an ordinary everyday life [20,33,34]. A number of these parents express that they are dependent on help from their social network to sustain their regular everyday life, and call for more and prolonged support to uphold their own parental capacity and avoid “hitting the wall” [7,35]. These families often find it difficult to ask for the help and support they actually need and they often experience that help and support drop shortly after the diagnosis and their network withdraws [7-9].

Previous research has found that network members surrounding families in crisis are generally positive in providing support but that they are often insecure about how to help. They report being afraid to say or do the “wrong things”, of intruding on the family, or they may assume that their contributions are unimportant or that the family copes adequately on its own [7,8,36]. Network members claim that by acknowledging support efforts and providing various strategies, professionals can facilitate better and more prolonged network support [36].

Most studies of social support related to cancer are descriptive, documenting the importance of social support for physical and psychological health as well as for quality of life [32]. Intervention studies on enhancing social support lag far behind, and are mostly directed to cancer patients, especially breast cancer, focusing on different kinds of support groups [37,38]. Intervention studies related to parental cancer and dependent children are lacking, as are intervention efforts aimed at enhancing social support for children and families members [39]. However, Hogan’s review [38] provides support for the overall usefulness of different social support interventions.

### Theoretical Framework

Social support is thought to affect mental and physical health positively through its influence on emotions, cognitions, and behaviors [6,38,40]. Nevertheless, the association between social support, well-being, and health is complex and therefore difficult to conceptualize. House and Kahn’s definition of social support makes a conceptual distinction between different types of social support, including emotional, economic and practical help, and the provision of information [41]. Social network support encompasses various kinds of support given to individuals and families by other family members, friends, colleagues, neighbors, and others [6,11]. Over the last decades, much health research has distinguished between “perceived” and “received” social support [6,42]. “Perceived support” refers to the perception by those who are in need of support that such support would be available if needed (ie, qualitative), whereas “received support” refers to the actual support resources received by those in need (ie, quantitative). Two major models have been proposed to explain the link between social support and well-being: the main or direct effect model and the buffering effect model [6,43]. The direct effect model suggests that social support is directly associated with well-being, while the stress buffering model describes how social support can protect individual well-being from the negative impact of stress. Perceived and received support have exhibited different effects on well-being and health, with perceived support demonstrating the most influential effect [6]. Furthermore, social support has been seen as transactional, which means that other factors (eg, personality characteristics, contextual, and interpersonal processes) influence the impact of the support. Nevertheless, exactly what the mechanisms are which provide for the effects of social support remains to be discussed and the causal links are still unclear [6,42].

Cohen [42] argues that strengthening and increasing the availability of support in social networks, and reducing negative interactions within one’s network are essential for human health. Psycho-education can be a viable strategy for achieving this. Psycho-education is defined as professionally delivered illness-specific information and tools for managing challenges in everyday life [44]. It builds on a holistic and competence-based approach, focusing on health promotion, collaboration, and empowerment where the development of open communication, competence, knowledge, and skills are crucial elements facilitating behavioral change [44]. Psycho-education looks to support the individual's understanding of a challenging situation and help gain access to resources, develop awareness of issues, foster a sense of control, and educate about coping skills for both families and their networks. These factors focus on improving cognitive awareness and coping skills. However, psycho-education also looks to promote insights that address affective worries and concerns [44]. This study focuses on investigating whether the psycho-education of social networks’ members is an appropriate method to achieve beneficial effects with respect to increasing social support and thereby parental quality of life, mental health and parental capacity, and thus the children’s well-being. Based on the theoretical framework we have developed a conceptual model of the study (Figure 1).

As shown in Figure 1, it is hypothesized that the Cancer-PEPSONE program will enhance the family’s social network support. This enhanced support will have direct effects on healthy parents’ quality of life, mental health, and parental capacity, as well as direct and indirect effects on children’s quality of life and mental health. The study upholds the child’s perspective and complies with the Norwegian Act for Health Personnel [45], putting children’s well-being on the agenda when living with parental illness. It also complies with the International Convention on the Rights of the Child (UN), emphasizing the rights of children to care, protection, rehabilitation, and assistance in various situations that can negatively affect their life situation.

**Figure 1 figure1:**
[figure not shown]
Research model.

### Objectives and Hypotheses

The purpose of the Cancer-PEPSONE project is to expand the knowledge base and build competence in networks to help children living with parental cancer. The overall aim of the study is to optimize social support from the social network through a psycho-educational intervention. Based on the project’s aims and research model, we hypothesize that (1) a psycho-educational program will improve the provisions of social support to the affected family, (2) parental psychosocial health and quality of life will increase through social network support, and (3) the children’s psychosocial health and quality of life will improve because of more and better social support and increased parental capacity, mental health, and quality of life.

## Methods

### Trial Design

Based on the study’s hypothesis and research questions, the Cancer-PEPSONE study will be conducted as a single center, randomized controlled trial (RCT) [46], including an intervention and a control group. This design is best suited to test the effectiveness of various types of intervention in clinical trials. The Cancer-PEPSONE study design is outlined in Figure 2.

After receiving written and oral information from one of the two first authors, families fulfilling the inclusion criteria are included in the study. The participants receive a form for informed consent and the first set of questionnaires for the healthy parent and one child in the family (T1) by mail. The consent form and the questionnaires are returned to the researchers in pre-stamped envelopes. Then, every other family is randomized to either the treatment group or the control group by one of the researchers based on the order in which the informed consent and questionnaires are returned. The type of intervention makes it impossible to blind the trial participants or the psychologist. The families in the intervention group and their network members receive the intervention, while the control group receives no intervention (care as usual). The control group is offered the intervention after finishing the study participation, after approximately 6 months, and all participating families get a DVD of the program after finishing T3 after 6 months.

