##### Data Collection

Healthy parents and the children fill out the entire dataset at inclusion (T1), after 3 months (approximately one months after the intervention for the intervention group), and after 6 months (Figure 2). One of the two first authors provides the families with questionnaires by post and they return them to the researchers in pre-stamped envelopes. The social network members in the intervention group fill out the T1 questionnaires prior to the meeting starting. The network members in the intervention group fill out the same questionnaires after 3 (T2) and 6 months (T3), distributed via the Internet and the website SurveyMonkey.

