### Results

The Cancer PEPSONE study is ongoing, where enrollment of families began in January 2014. As of October 2015, 45 families are enrolled in the study. Of those families, 19 are randomized to the intervention group, with 15 families receiving the intervention together with approximately 120 network members, while 4 families are waiting for the intervention. As well, 20 families are enrolled in the control group and 6 families are not yet randomized. The first results from the study are expected in October 2015.

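### Families are allocated by alternation in order of returned forms, by a member of the research team, so the trial is quasi-randomized rather than randomized as described

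*Protocol article*

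**What the plan says.** The abstract and the Trial Design section of the protocol article present the study as a randomized controlled trial with an intervention and a control group. Trial Design then gives the allocation method: "every other family is randomized to either the treatment group or the control group by one of the researchers". The same sentence says what determines the sequence, namely that assignment is "based on the order in which the informed consent and questionnaires are returned".

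The steps around allocation are also described:
- Information and inclusion: "After receiving written and oral information from one of the two first authors, families fulfilling the inclusion criteria are included in the study".
- Mailing (Data Collection): "One of the two first authors provides the families with questionnaires by post".
- Return: "The consent form and the questionnaires are returned to the researchers in pre-stamped envelopes".
- Assignment follows, by one of the researchers.

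Trial Design adds that neither participants nor the psychologist can be blinded. The outcome section says that the measures are self-reported questionnaires. The Results section gives the position in October 2015: 45 families enrolled, 19 allocated to intervention, 20 to control, and "6 families are not yet randomized".

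No section mentions a chance-based sequence, an independent allocator or any concealment step.

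**The concern.** Taking every second family in order of return leaves nothing to chance, so the method contradicts the name given to the design. The rule is also visible to the people who operate it. The team that informs families and posts their questionnaires also receives the returns and makes the assignment. When an envelope is opened and logged, the next arm is already known, and that envelope contains the family's T1 answers on support, distress and quality of life. If two returns are at hand together, the order of logging decides which family gets which arm.

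Every between-group comparison in the trial depends on this step. If families with better prospects were steered towards one arm, even unintentionally, the difference would be carried into outcomes that unblinded participants report themselves. The Discussion plans guidelines for the local healthcare system if results are favourable, so the strength of the design should be described accurately.

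**Working it through.** **Counts.** The Results figures are consistent: 19 + 20 = 39 allocated, and 39 + 6 = 45 enrolled. The planned total is 60 families, 30 per arm.

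**Is there a chance element?** The rule has two inputs: the arm given to the previous family, and the order of return. Neither is a random draw made by the trial. To read the sentence as true randomization, one would have to disregard both the every-other wording and the statement that order of return is the basis.

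**How predictable is the next assignment?**
- Alternation allows 2 sequences, one for each starting arm. After the first family the rest is fixed: 59/60 = 98% of assignments are certain. If the starting arm is set in advance, 60/60 are certain.
- Simple randomization: 0% certain, and 50% correct by guessing.
- For comparison, take a random list in fixed blocks of size 2m, with block size known and past assignments visible. The share known with certainty is 1/(m + 1). Blocks of 4 (m = 2) give 1/3 = 33%, and blocks of 6 (m = 3) give 1/4 = 25%. Best-guess accuracy is 71% and 68%.
- With a random list concealed from recruiters, with block sizes varied at random, the next assignment is not visible to them.

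**When does that foreknowledge apply?**
- At receipt and logging it is complete from the second family on.
- While a family is being informed or sent its forms, its arm depends on whether an odd or even number of other returns is logged before its own. Staff may be able to influence that, but the post also decides it, so foreknowledge is partial.

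**What does the order of events protect?** Consent and T1 completion precede assignment. Families therefore cannot refuse, or colour their baseline answers, because of the arm they received. T1 scores also allow imbalance on the measured outcomes to be seen and adjusted for. Neither feature controls the order in which returns are logged, or differences that the questionnaires do not capture.

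**The case against.** The best defence is that the order of postal returns is close to haphazard. Families come from many sources (Recruitment section), so the team does not control who arrives or when. They consent and complete T1 before any arm is assigned. The article does not say that the allocating researcher is the person who informs families, only that both belong to the research team. Nor does it say that anyone delayed, pursued or reordered returns. The Intervention section adds that no researcher takes part in delivering the program. All of this stands. It lowers the likely amount of bias, but it does not turn alternation into randomization or conceal the next arm from the person assigning it.

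A condensed article may leave detail to the full protocol. That allowance does not apply here, because the method is stated and it conflicts with the label.

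Some stronger inferences go beyond the document:
- A reader might take the 19 to 20 split as confirmation of strict alternation. It is compatible with it, but under simple randomization of 39 families the probability of a split that close is 2 × C(39,19)/2^39 = 0.25, and blocked randomization could also give it. The quoted rule carries the point.
- A reader might infer that every family's arm is known from first contact. That holds only at receipt and logging.
- A reader might conclude that selection bias could never be distinguished from an effect. T1 scores allow measured imbalance to be examined; only unmeasured imbalance stays hidden.
- A reader might conclude that the planned tests are void. The article plans t tests, regression and structural equation models, which are model-based. Alternation weakens their causal interpretation but does not invalidate the calculations.

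**Conclusion.** The point holds. The allocation described is alternation, which is quasi-random and unconcealed, and it contradicts the description as a randomized trial. The certain part is its predictability: 59 of 60 assignments, or all 60 with a fixed starting arm, are known to the allocating researcher at receipt and logging. The size of any resulting bias cannot be derived from the document, and there is no evidence that selective ordering took place.

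The method applies to the 39 families already allocated, on the assumption that the stated rule was followed. That is 39/45 = 87% of those enrolled in October 2015, or 39/60 = 65% if recruitment reaches its target. Only 6 families are documented as still unallocated. A further 60 − 45 = 15 would bring the number open to randomization to 21, but this assumes that enrolment continues, whereas Table 1 shows enrolment ending in spring 2015.

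**What to change.** 1. For every family not yet allocated (the 6 documented and any recruited later), use a computer-generated 1:1 list in blocks of randomly varying size. Someone in the research group without family contact should hold it and release each assignment only after that family's consent and T1 forms are logged.
2. Submit the change as an amendment to the ethics committee and the data services body, the route given under Ethical Implications and Risk.
3. Describe the 39 families already allocated as assigned by alternation (quasi-randomized), and correct the randomized description in the abstract and methods.
4. Estimate group differences with adjustment for the T1 value of the outcome, which is already collected. This addresses measured baseline imbalance only.

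The cost is one amendment and one list, with no additional families, visits or questionnaires. The real price is in reporting: the paper must say that most families were alternated, and later randomization of the remainder cannot undo that. If recruitment has stopped, step 1 affects at most the 6 waiting families, and steps 3 and 4 still apply.
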